### Causal effects of interest

The primary causal effect in our study is the intention-to-treat effect. That is the comparative effect of being assigned to the CAD screening strategies at inclusion, regardless of whether the individuals continue following the strategies during follow-up. The per-protocol effect will also be investigated after exclusion of participants from the control group who underwent routine CAD screening during follow-up.

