### Recruitment of participants and follow‑up

Data will be extracted from 1 January 2008 to 31 December 2019. The screening period will cover the 7 years from 1 January 2008 to 31 December 2014, which will allow us to identify patient eligibility criteria. All patients identified in the SNDS databases during the pre-selection period who met the inclusion criteria will be recruited in the study from 1 January 2015 to 31 December 2015. Participants will be followed for 4 years, until 31 December 2019 (Fig. 1).

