### Outcomes

The primary outcome is the incremental cost per life-year gained over 4 years in CAD routine screening group versus no screening in the perspective of French health insurance. The key secondary health economic endpoints include the cost-consequence analysis linking the total 4-year direct costs of each strategy and clinical endpoints; an analysis of budget impact for the French Insurance system to promote the routine CAD screening; and the total care consumption during follow-up. The key secondary clinical endpoints included the effects of CAD screening (versus no screening) in terms of major adverse cardiovascular events (a composite of acute coronary syndrome, coronary revascularization, or hospitalization for heart failure); all-cause mortality; major cerebrovascular events (a composite of stroke, hospitalization for TIA, or carotid revascularization); major adverse limb events (a composite of ischemic diabetic foot, lower-limb revascularization or amputation); and CKD or end-stage kidney disease (ESKD, requirement of any sustained haemodialysis or kidney transplantation). Each component of these composite endpoints will also be considered individually. Major cerebrovascular events, major adverse limb events and ESKD will be assessed during follow-up among participants without a baseline history of each condition (as appropriate). Finally, SCADIAB will also assess the frequency of routine CAD screening, expressed as the number of examinations performed yearly per individual.

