### Statistical analysis

The gross estimate of the incremental cost per life-year gained at 4 years will be conducted. High dimension propensity score will be used to balance the baseline characteristics of participants. Comparisons between study groups will be performed without adjustment; and with adjustment for confounding factors using the weighted by inverse probability of receiving treatment (IPTW). A cost-consequence analysis will be performed linking results of all direct costs, and results on major cardiovascular events. A budget impact analysis will be conducted to determine the public expenses of the spread of a routine CAD screening at 5 years from French health insurance perspective. The risk of clinical outcomes by study groups will be assessed using IPTW proportional hazards survival regression models. We will also consider the competing risk of all-cause death.

We will perform subgroup analyses by sex, age and frequency of CAD tests. Finally, a sensitivity analysis is planned to assess the interest of routine CAD screening in T2DM people with at least 2 cardiovascular risk factors without microvascular or macrovascular disease.

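### The per-protocol rule removes whole control participants because of a later CAD test, which biases the per-protocol mortality and life-year estimates, usually in favour of screening

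*Protocol article*

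**What the plan says.** The Protocol article names two causal effects in Causal effects of interest. The first has priority: "The primary causal effect in our study is the intention-to-treat effect". The second, the per-protocol effect, is defined by a deletion rule: it is to be "investigated after exclusion of participants from the control group who underwent routine CAD screening" during follow-up.

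The window in which a control can be tested, and so deleted, comes from Recruitment of participants and follow-up: "Participants will be followed for 4 years, until 31 December 2019". The section Outcomes makes life-years the denominator of the main result ("The primary outcome is the incremental cost per life-year gained over 4 years in CAD routine screening group versus no screening") and lists all-cause mortality as a key secondary clinical endpoint. MACE is "a composite of acute coronary syndrome, coronary revascularization, or hospitalization for heart failure", and each component is also analysed separately.

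The adjustment is described in Statistical analysis: "High dimension propensity score will be used to balance the baseline characteristics of participants", followed by IPTW comparisons and IPTW proportional hazards models. The article mentions neither censoring at the deviation nor weights that change over time.

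**The concern.** The rule decides who belongs to the control arm at time zero from something that happens later. Deletion requires the control to live until the test. Controls who die untested can never be deleted, whereas controls who live long have more time in which to be tested and removed. The retained control arm therefore has too high a death rate even if screening does nothing.

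Weights built from baseline characteristics do not help, because the selection is made after baseline, in one arm, on a variable that depends on survival.

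The per-protocol effect is one of only two effects named, and survival feeds both a key secondary endpoint and the denominator of the cost-effectiveness ratio. A per-protocol survival difference produced by the deletion rule could be read as evidence about screening.

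**Working it through.** The article gives no mortality rate, crossover rate or sample size, so there is no figure of its own to reproduce. The question is what the rule returns when the true effect is nil.

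**Inputs.** From the article: T = 4 years; whole-participant exclusion in the control arm; baseline weighting only. Assumed: death hazard L = 0.05 per year (range 0.03 to 0.07); control testing hazard m, constant and, to begin with, unrelated to prognosis. The screening arm is given the true death rate L, and no confounding is assumed.

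**Closed form.** Let k = L + m.

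- Controls who die untested: D = (L/k)(1 − e^(−kT))
- Controls alive and untested at T: S = e^(−kT)
- Risk among those kept: D/(D + S)
- Person-time of those kept: P = L[(1 − e^(−kT))/k² − T·e^(−kT)/k] + T·S
- Rate ratio, screening versus kept controls: L/(D/P)

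Suppose 30% would be tested over 4 years in the absence of death. Then m = −ln(0.70)/4 = 0.0892, k = 0.1392, S = 0.573, D = 0.153 and P = 2.571.

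- Kept-control 4-year mortality = 0.153/0.7265 = 21.1%, against a true 1 − e^(−0.2) = 18.1%
- Kept-control death rate = 0.1534/2.571 = 0.0597; rate ratio = 0.0500/0.0597 = 0.84
- Life-years = 2.571/0.7265 = 3.539, against a true (1 − e^(−0.2))/0.05 = 3.625; spurious gain 0.087

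With 10, 20, 30, 40, 50 or 60% tested, the ratio at L = 0.05 is 0.95, 0.90, 0.84, 0.77, 0.70 or 0.63. It barely changes for L between 0.03 and 0.07. Across that grid the spurious gain runs from 0.015 to 0.33 life-years.

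**Simulation on the article's calendar.** Entry is uniform over 2015, controls can be tested from 1 January 2016, follow-up is 4 years from entry, L = 0.05, and there are 2,000,000 controls per row.

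| Tested per year (assumed) | Controls deleted | Rate ratio | Spurious life-years |
|---|---|---|---|
| 5% | 15% | 0.91 | 0.05 |
| 10% | 28% | 0.82 | 0.10 |
| 15% | 39% | 0.73 | 0.16 |

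At 10% per year, deleted controls have 4-year mortality of 9.1% and kept controls 21.6%. These average back to the truth: 0.278 × 9.1% + 0.722 × 21.6% = 18.1%. When the same controls are kept and censored at the test date, the death rate is 0.050, the true value.

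**Testing that depends on prognosis.** Two null stress tests were run.

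- *Fixed high-risk class:* 30% of controls, tested 5 times as often and dying 2 to 5 times as fast. The mortality risk ratio was 0.87 to 0.98, and the life-year gain stayed positive.
- *Illness-death model:* illness raises both testing and mortality, and 30% of controls are deleted. The risk ratio exceeded 1 in 3 of 30 scenarios (1.02 to 1.11), all with mortality raised 10-fold and testing 10- to 20-fold. The life-year gain was positive in all 30 (0.016 to 0.091).

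In the fixed-class setting, censoring plus inverse-probability weights gave risks of 17.6, 17.7 and 17.0%, against true values of 17.6, 17.6 and 17.1%.

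**Revascularization.** Assume a background rate of 1% per year, 20 or 40% of controls tested over 4 years, and 2 to 10% of tests leading to a procedure. The 4-year risk is 3.9 to 7.0% in all controls and about 3.5% in those kept. Most of that gap is what any never-screened comparison removes: the never-tested risk under these assumptions is (0.01/0.06)(1 − e^(−0.24)) = 3.6%. The remaining shortfall is small and lowers the control risk, so it runs against screening.

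**The case against.** The strongest defence is one of scope. The intention-to-treat effect is primary, the per-protocol effect is additional, and the deletion rule touches neither the intention-to-treat cost per life-year nor the main IPTW analysis. This stands, and it limits the severity.

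The second defence is that tested controls are likely to be sicker, which offsets the bias. This stands in part. It shrinks the bias and, with very strong illness-triggered testing, reverses it for the mortality risk ratio. It does not make the estimate valid.

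Three stronger readings are tempting, and the article does not support them.

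- *The rule creates a benefit of screening on every endpoint.* MACE contains revascularization. Deleting tested controls also deletes their procedures and their test and downstream costs. The net effect on MACE and on the cost-effectiveness ratio has not been shown and may go against screening.
- *The rule is faulty because it treats only one arm.* Under Screening strategies and study allocation, one test places a patient in the screening group at the date of that test. If the strategy is a single test, everyone in that arm has complied at inclusion. Whether departures are possible depends on a definition that the article does not give.
- *The result would appear to confirm the intention-to-treat finding.* That finding is unknown.

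It cannot be said that the matter is merely left to the analysis plan: the article states the rule outright.

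**Conclusion.** As stated, the rule does not estimate a per-protocol effect on all-cause mortality or life-years. It selects controls on having survived to be tested, and baseline IPTW cannot repair that. The bias usually favours screening: a rate ratio of about 0.91, 0.82 or 0.73 and about 0.05, 0.10 or 0.16 spurious life-years under a true null. Those sizes rest on assumed mortality of 5% per year, assumed testing of 5, 10 or 15% per year, and testing unrelated to prognosis. They illustrate the problem and do not predict this study's result. For MACE, coronary revascularization and costs, the per-protocol estimate is likewise invalid, with no established direction. Because the primary intention-to-treat effect is unaffected, this should be fixed but is not critical to the main result.

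**What to change.** Drop the exclusion rule. Keep every control, censor each at the date of the first CAD screening test, and weight the remaining person-time by the inverse probability of remaining unscreened, modelled on baseline and time-updated covariates from the claims data. Use the same weighted follow-up for the per-protocol life-years and costs. If the screening strategy is meant to be sustained, say so and state what counts as a departure in that arm.

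The cost is a change of wording plus a time-varying weight model on claims already planned for extraction. The price is wider intervals and reliance on measured time-varying confounders.

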### Statistical analysis

The gross estimate of the incremental cost per life-year gained at 4 years will be conducted. High dimension propensity score will be used to balance the baseline characteristics of participants. Comparisons between study groups will be performed without adjustment; and with adjustment for confounding factors using the weighted by inverse probability of receiving treatment (IPTW). A cost-consequence analysis will be performed linking results of all direct costs, and results on major cardiovascular events. A budget impact analysis will be conducted to determine the public expenses of the spread of a routine CAD screening at 5 years from French health insurance perspective. The risk of clinical outcomes by study groups will be assessed using IPTW proportional hazards survival regression models. We will also consider the competing risk of all-cause death.

We will perform subgroup analyses by sex, age and frequency of CAD tests. Finally, a sensitivity analysis is planned to assess the interest of routine CAD screening in T2DM people with at least 2 cardiovascular risk factors without microvascular or macrovascular disease.

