### Study design

The study design and protocol have been published in a previous issue of this journal [13]. We report here updated methods and statistical approach that will be performed in this study, namely the emulation of a 2-arm randomised target trial using the French electronic health record (SNDS, *Système National des Données de Santé*), a claim database encompassing the whole French population [14, 15].

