### Screening strategies and study allocation

Each patient will be assigned into one of the two study groups according to the CAD screening strategy performed during the recruitment period. Patients who had at least one CAD screening test will be assigned to the routine CAD screening group and included at the time of the first CAD test. Patients who did not perform any CAD screening (except for the resting electrocardiogram) will be assigned to the control group, and included at the time of the resting electrocardiogram, or at the time of a medical visit (general practitioner, diabetologist, or cardiologist), whichever comes first.

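### The adjusted cost difference rests wholly on propensity-score weighting: the article names no outcome model for cost and no use of patients' earlier cost

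*Protocol article*

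**What the plan says.** - **Primary outcome** (Protocol article, Outcomes): "The primary outcome is the incremental cost per life-year gained over 4 years in CAD routine screening group versus no screening". The cost difference is the numerator of this ratio.
- **Estimation** (Statistical analysis): "The gross estimate of the incremental cost per life-year gained at 4 years will be conducted", then "High dimension propensity score will be used to balance the baseline characteristics of participants". Comparisons are made unadjusted and "with adjustment for confounding factors using the weighted by inverse probability of receiving treatment (IPTW". For clinical outcomes the section names weighted proportional hazards models. For cost it names no model.
- **Allocation** (Screening strategies and study allocation) is observational: "Each patient will be assigned into one of the two study groups according to the CAD screening strategy performed during the recruitment period".
- **Data** (Study design; Recruitment of participants and follow-up): the source is "a claim database encompassing the whole French population", and "Data will be extracted from 1 January 2008 to 31 December 2019". The only use stated for the years 2008 to 2014 is that they are the period "which will allow us to identify patient eligibility criteria".

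The article does not list the covariates in the score, does not say whether earlier cost or utilisation is among them, and gives no balance criterion.

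**The concern.** Having a coronary test in 2015 is an act of care use. It is reasonable to expect that patients who used more care before 2015 were both more likely to be tested and more costly afterwards. Earlier reimbursed cost is the baseline value of the cost outcome and the most direct measure of that tendency.

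With weighting as the only adjustment, any imbalance in earlier cost that survives the weighting passes into the cost difference, and nothing else in the stated analysis would catch it. It then enters the primary ratio, the cost-consequence analysis and, where these costs feed it, the budget impact analysis. Because cost varies widely between patients, an imbalance that looks small in standardised units can be large in euros.

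**Working it through.** **1. What can be reproduced.** The article states no sample size, cost SD, screening cost or balance threshold, so there is no planned figure to recompute. All euro values below are assumptions.

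**2. Whether earlier cost should be available.** Extraction starts on 1 January 2008 and inclusion runs through 2015, so at least seven calendar years precede any inclusion. In a claims source, prior-year reimbursed cost should be constructible. This is an inference from source and dates; the article does not say so.

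**3. Size of residual bias.** If weighting leaves an SMD of d in earlier cost, and earlier cost has correlation ρ with 4-year cost, then approximately

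bias ≈ ρ × SD × d

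| Case | ρ | SD (EUR) | d | Bias (EUR) |
|---|---|---|---|---|
| Lowest | 0.3 | 10,000 | 0.02 | 60 |
| Middle, small imbalance | 0.5 | 20,000 | 0.02 | 200 |
| Middle | 0.5 | 20,000 | 0.05 | 500 |
| Middle, imbalance at 0.1 | 0.5 | 20,000 | 0.10 | 1,000 |
| Highest | 0.7 | 40,000 | 0.10 | 2,800 |

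**4. Check by simulation.** One data set of 200,000 patients, of whom 54,131 were screened. A code summary Z and a separate component U (independent standard normal) set the log of earlier cost as 0.9 × (0.8Z + 0.6U), rescaled to an SD of 5,000 EUR. The logit of screening was −1.0 + 0.2Z + 0.10U. Four-year cost was twice earlier cost, plus gamma noise (shape 0.5, mean 8,000 EUR), plus 400 EUR if screened. This gave SD 15,084 EUR and ρ = 0.66.

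| Analysis | Estimate (EUR), truth 400 |
|---|---|
| Weighting on Z only | 911 |
| Weighting on Z only, plus regression on earlier cost | 502 (SE 51) |
| Weighting on Z and earlier cost | 489 |
| Weighting on Z and earlier cost, plus regression on earlier cost | 507 (SE 51) |

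With weights from Z only, the SMD of Z was 0.000 and that of earlier cost 0.041, below the customary 0.1. The formula gives 0.6645 × 0.0409 × 15,084 ≈ 410 EUR, and 911 − 502 = 409 EUR. The remaining 102 EUR (502 − 400) is about two standard errors.

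Row two is the case for the change: the outcome model recovers what a score without earlier cost misses. Rows three and four show that when the score already holds earlier cost, the extra step moves the estimate by only 507 − 489 = 18 EUR.

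**5. Does a rich score make this unnecessary?** That depends on the assumptions. In one set of simulations (8,000 patients, 40 runs, true difference 600 EUR, ρ about 0.45, earlier cost not in the score), bias fell from about 2,300 EUR with 6 codes to 560 with 50 and 160 with 200. Under other assumed inputs with 150 codes, weighting on codes alone gave 2,511 EUR against a true 600, an excess of 1,911. Augmented weighting with earlier cost in the outcome model gave 924, an excess of 324. The change removed (2,511 − 924) / 1,911 = 83% of the excess. The rest reflects care intensity that earlier cost does not record, and the fix does not cure it.

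**6. What the estimator costs if earlier cost is already in the score.** Under those same inputs, plain and augmented weighting differed by 33 EUR (908 and 941), with standard errors of 365 and 348. In a further simulation (8,000 patients, 400 runs, truth 600) they gave 616 and 638 EUR, with standard errors of 619 and 617. Nothing is lost, and the gain in precision is small at most.

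**The case against.** The strongest reply is that this is a short update article. The design and protocol were published earlier, and a covariate list, a balance threshold and the details of a cost model are what such an article leaves to the full plan. A high-dimensional score may well contain earlier cost or utilisation. Weighting on such a score is an accepted way to adjust claims data, and once earlier cost is in the score a doubly robust estimator hardly changes the answer (steps 4 and 6).

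Most of this stands. Not listing the covariates is no defect, and choosing inverse probability weighting is not an error. What does not fall away is the method that the article itself sets out as its updated statistical approach: weighting is the only adjustment named, and cost, half of the primary outcome, gets no second line of defence.

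Two stronger readings are tempting, and the document supports neither.

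- **That the score is built from codes alone and leaves earlier cost out.** A reader might infer this because the pre-inclusion years are mentioned only for eligibility. The article neither includes nor excludes earlier cost.
- **That an imbalance passing routine checks would exceed the cost of screening.** The article states neither a screening cost nor a balance rule. Over the 36 combinations of SD (10,000, 20,000, 30,000 or 40,000 EUR), ρ (0.3, 0.5 or 0.7) and d (0.02, 0.05 or 0.10), the bias exceeds an assumed 300 EUR in 23 and an assumed 1,000 EUR in 8. These counts describe the grid and are not probabilities.

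**Conclusion.** The point holds as a worthwhile, nearly free improvement to a stated analysis choice, and not as a demonstrated error. As written, the adjusted cost difference depends entirely on the propensity score, in a design where care use determines the group and earlier care use probably predicts the outcome.

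The size is uncertain: 60 to 2,800 EUR per patient across the assumed ranges, and less if the score is rich in good proxies for care intensity. If earlier cost is already in the score and balanced, most of this bias is gone, and the change mainly guards against a misspecified score, with a small gain in precision. The conclusion rests on three things that the article does not state: that care intensity influences screening, that earlier cost predicts later cost to the assumed degree, and that earlier cost can be built from the extraction. Confidence is medium.

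**What to change.** - Make the main adjusted estimate of incremental cost and life-years doubly robust: augmented inverse probability weighting, or a weighted outcome model with standardisation (a log link would suit skewed cost).
- Put prior-year reimbursed cost and prior-year hospital days, measured up to the inclusion date, in the outcome model. Add them to the propensity score if they are not already there.
- Report the balance of both after weighting.
- Bootstrap cost and life-years jointly, so that the uncertainty of the ratio reflects their dependence.
- Keep plain inverse probability weighting as a sensitivity analysis.

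If earlier cost is already in the score, one sentence saying so settles that part. The rest needs analysis-plan wording and modest programming. It should need no new data, since the claims extraction already covers the years before inclusion, and it loses no patient.

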## Background

Type 2 diabetes mellitus (T2DM) is a substantial health problem with a high clinical and economic burden [1, 2]. Despite a recent prognostic improvement, coronary artery disease (CAD) remains one of the leading causes of mortality in people with T2DM [3]. CAD is often severe and silent in patients with T2DM [4], prompting screening in asymptomatic individuals. Previous randomised controlled trials (RCTs) have failed to provide evidence of the effectiveness of routine CAD screening in reducing major cardiovascular events and mortality in people with T2DM at moderate to high cardiovascular risk [5–9]. However, doubts remain about T2DM patients at a very high cardiovascular risk, who can benefit from this screening strategy, but in whom trials have not yet been conducted. Despite this lack of concrete evidence, current clinical practice and guidelines recommend routine CAD screening for silent CAD in individuals with diabetes at high cardiovascular risk [10]. The widespread practice CAD screening results in significant healthcare costs due to invasive testing, revascularisation procedures, and intensified pharmacological therapies. The cost-effectiveness of routine CAD screening has not been prospectively evaluated in T2DM people. Only two economic studies based on Markov models have addressed this issue by comparing screening versus no screening strategy in Japanese and American populations [11, 12]. The results of these studies were inherently limited by assumptions inherent in the models, uncertainties in the epidemiological and cost data, and variations in health care costs between countries.

In the midst of this discrepancy between the lack of tangible evidence and clinical practice, we are conducting the Cost-effectiveness of Screening of Coronary Artery disease in patients with type 2 DIABetes at a very high cardiovascular risk (SCADIAB) study to estimate the cost-effectiveness of routine CAD screening in T2DM patients with a very high cardiovascular risk.

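### For major adverse cardiovascular events and their coronary components, and possibly all-cause mortality, the named proportional hazards model is doubtful by design, so a single 4-year hazard ratio could hide opposite early and late effects

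*Protocol article*

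**What the plan says.** All references are to the protocol article.

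- **Statistical analysis** names one effect model for the clinical outcomes: "The risk of clinical outcomes by study groups will be assessed using IPTW proportional hazards survival regression models". It adds: "We will also consider the competing risk of all-cause death". It names no time-specific risk, restricted mean or time-varying effect.
- **Screening strategies and study allocation** sets time zero for screened patients: they are "assigned to the routine CAD screening group and included at the time of the first CAD test". Controls start at a resting electrocardiogram or a medical visit.
- **Background** says that widespread screening "results in significant healthcare costs due to invasive testing, revascularisation procedures, and intensified pharmacological therapies".
- **Outcomes** defines major adverse cardiovascular events (MACE) as "a composite of acute coronary syndrome, coronary revascularization, or hospitalization for heart failure", and adds: "Each component of these composite endpoints will also be considered individually". All-cause mortality is a further key secondary endpoint. The primary outcome is cost per life-year gained over 4 years.

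**The concern.** A proportional hazards model with one arm term assumes that the hazard ratio is the same in the first month as in the fourth year. Here three stated features work against that for MACE. The clock starts at the test in one group only, a positive test can lead to revascularization, and that procedure is itself an event. Test-triggered procedures can be expected to cluster just after time zero among screened patients. Controls start at a visit with no such trigger. Any benefit of the resulting procedures or drugs cannot come before those treatments.

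If the hazard ratio is above 1 early and below 1 later, the fitted ratio is a weighted average of the two. It then depends on where follow-up stops, and it can sit near 1 although the groups differ clearly in both periods. A reader could take that as no effect. It matters most for MACE because the cost-consequence analysis sets costs against these events.

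**Working it through.** **Nothing to reproduce.** The article states no event rate, hazard ratio, sample size or power for the clinical outcomes. Every input below except the 4-year horizon is an assumption.

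**Assumed inputs, main scenario**
- Control hazard 0.04 per year, constant.
- Screened group: an extra 3% of patients have a triggered event in months 0-3. Added hazard = −ln(1 − 0.03)/0.25 = 0.122 per year, so the early hazard is 0.162 and the early hazard ratio about 4.05.
- Hazard ratio after 3 months 0.8, so the later hazard is 0.032 per year.
- 5,000 patients per group, censoring only at the end of follow-up.

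**Cumulative risks**, from 1 − exp(−cumulative hazard):

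| Time | Control | Screened | Difference (points) |
|---|---|---|---|
| 3 months | 1 − exp(−0.0100) = 1.0% | 1 − exp(−0.0405) = 4.0% | +3.0 |
| 1 year | 1 − exp(−0.0400) = 3.9% | 1 − exp(−0.0405 − 0.032×0.75) = 6.2% | +2.3 |
| 4 years | 1 − exp(−0.1600) = 14.8% | 1 − exp(−0.0405 − 0.032×3.75) = 14.8% | about 0 |

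**What a single Cox ratio would report.** Setting the expected score of the one-term model to zero gives its large-sample value, which changes with the end of follow-up:
- 1 year: 1.63
- 2 years: 1.22
- 4 years: 1.02

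**Power at 4 years**, two-sided 5%, from Φ(√(D/4)·|ln HR| − 1.96) plus the small opposite tail, where D is the expected number of events:
- Single hazard ratio, D about 1,480: 6%.
- Period after 3 months, D about 1,233, HR 0.8: √(1,233/4) × 0.223 = 3.92, so Φ(1.96) = 97%.
- Risk difference at 4 years alone: 5%.

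Mean event-free time over 4 years is about 21 days shorter in the screened group, although the 4-year risks are equal.

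**Other assumed patterns**
- 2% per year, 2% early excess, later HR 0.7, 2,000 per group: single HR 0.98, power about 5%, against about 80% for the later period.
- 4% per year, 1% early excess, later HR 0.7, 2,000 per group: power 79% against 97%. The single ratio still works here.
- Control 4-year risk 10-30%, screened share 20% or 50%: HR 3 for 3 months then 0.85 gives a Cox HR of 0.99-1.01; HR 2 for 6 months then 0.8 gives 0.96-0.97; HR 1.5 for 6 months then 0.85 gives 0.94.
- Delayed benefit without early excess, same ranges: HR 1.0 for year 1 then 0.8 gives 0.85-0.86. This is dilution, not cancellation.

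**The case against.** **The article does not say that the hazard ratio is the only summary.** This is correct. A reader might infer that every clinical outcome will be reduced to one constant ratio, but the text does not say so. It plans competing-risk and component analyses, and checks of proportionality may sit in an analysis plan that is not shown. The point therefore does not rest on a missing diagnostic. It rests on the stated model fitting poorly to stated design features. Component analysis does not remove it, since revascularization alone should show the strongest early excess.

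**It does not extend to all outcomes.** A reader might infer the same problem for cerebrovascular, limb and kidney outcomes. The article gives no reason for opposite early and late effects there. For mortality the argument is conditional: it needs an early procedural risk or a delayed benefit, and the article states neither.

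**The primary outcome is not touched.** A reader might infer that a misfitting hazard ratio would distort the life-years. Nothing says that life-years will be derived from it.

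**The alternatives are not uniformly better.** This also stands. In the main scenario the 4-year risk difference is as null as the hazard ratio (5% against 6% power). Restricted mean time detects the net loss in the main scenario (88% power) but has only 33% in the scenario with a 1% early excess, where the hazard ratio has 79%. The late-period contrast answers a different question from the overall ratio, so its higher power does not show that the overall ratio loses most of the information. These measures belong beside the hazard ratio, not in its place.

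**The scenarios are chosen.** Two of the three early-excess scenarios nearly cancel by construction. They show that cancellation can happen, not that it will.

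**Conclusion.** The point holds for MACE and its coronary components, above all coronary revascularization, and possibly for all-cause mortality. An early excess of MACE follows from the article's own time zero, its Background statement and its event definition. That effects will cross is not established, because the later benefit is an assumption.

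The size is illustrative only. Under a strong early excess with later benefit, the single ratio drifts from 1.63 at 1 year to 1.02 at 4 years. Across the milder crossing patterns it ends between 0.94 and 1.01. Under delayed benefit alone it is diluted from 0.8 to about 0.85. The finding concerns secondary endpoints. It is worth acting on because the remedy is cheap and takes nothing away from the plan.

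**What to change.** In Statistical analysis, for MACE, its coronary components and all-cause mortality, keep the weighted hazard ratio and add:

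1. IPTW-weighted cumulative incidence curves, with death as a competing event for non-fatal outcomes, and risk differences at several fixed times (for example 3 months, 1 year and 4 years). The 4-year time point alone is not enough.
2. An arm-by-period term in the weighted hazards model (for example 0-3 months and after).
3. For all-cause mortality, the IPTW-weighted difference in restricted mean survival time at 4 years, which is in the same unit as the primary life-years.

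The cost is a few lines of analysis-plan wording and modest extra computation on the same data and weights. The downside is more than one number per outcome. Period-specific hazard ratios also need cautious reading, because later periods include only patients still event-free.
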